**Study status**

The focus group discussions and in-depth interviews have been completed, with Phase 1 analysis finalised in September 2022. Phase 2 of the study, including application development and pilot testing, was conducted from October 2022 to August 2023, with the pilot study completed in September-October 2023. Phase 3 of the study, which will determine the effectiveness of the refined application, is scheduled to commence in October 2023 and continue through March 2025.

**Dissemination**

We will be disseminating the results of the study in the form of conference presentations and as manuscripts.

## Potential strengths and limitations

The community-based rural hypertension intervention features several notable strengths, including its cluster randomisation approach ensuring real-world applicability, user-centred design with continuous refinement through an Agile framework, multilingual accessibility in both English and Kannada, and comprehensive self-management tools covering BP tracking, medication reminders, lifestyle coaching, and emergency alerts.

Despite these strengths, the intervention faces several significant limitations. Our inclusion criteria requiring smartphone ownership introduce significant selection bias by excluding participants who cannot afford smartphones or are less technologically literate. This bias is particularly concerning as it excludes potentially vulnerable populations who might derive the most significant benefit from accessible hypertension management tools. While smartphone penetration in Karnataka exceeds 60% overall, ownership varies substantially by socioeconomic status, age, and rural versus urban location, with rural households earning less than ₹15,000 monthly showing ownership rates of approximately 30-40%. This means our findings may not be generalisable to a substantial portion of the hypertensive population, particularly those from lower socioeconomic backgrounds. Additionally, by limiting participation to existing smartphone users, our intervention inherently selects for already technologically comfortable individuals, potentially overestimating the real-world effectiveness of mHealth interventions when deployed across diverse populations with varying digital literacy levels.

Other limitations include potential adherence issues, which will be addressed through regular follow-up calls and push notifications to maintain engagement. Loss to follow-up will be minimised through strategic incentives, such as providing blood pressure monitors to participants who demonstrate compliance with the study protocol. While this study addresses hypertension management challenges relevant across India, our findings will primarily apply to Kannada-speaking populations in coastal Karnataka. India’s remarkable linguistic diversity, varying smartphone penetration rates across states, and distinct regional healthcare practices may limit the direct application of our intervention to other regions without appropriate cultural and linguistic adaptations. However, the Agile development methodology and user-centred design principles we employ provide a replicable framework that can be adapted for other Indian states and linguistic communities.

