## Abstract

**Background:**

Hypertension is a significant risk factor for cardiovascular disease, contributing to global mortality and disability. Approximately 30% of Indian adults are diagnosed with hypertension. Evidence supports that self-monitoring and blood pressure self-management can lower systolic BP by an average of 3.2 mmHg. mHealth applications facilitate remote monitoring and self-management, yet existing applications in India lack customisation for user needs, limiting their usability. This study aims to develop and evaluate a novel, user-friendly mHealth application tailored to hypertensive individuals.

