## Introduction

Hypertension is a significant public health concern worldwide, with an increasing prevalence in both urban and rural communities. It is a leading cause of cardiovascular diseases such as myocardial infarction, stroke, and kidney disease, contributing significantly to global mortality and morbidity. In India, recent estimates suggest that hypertension affects between 15% and 35% of the population, with poor awareness, treatment, and control rates despite its high prevalence (
Gupta et al., 2024). A study by
Ramakrishnan et al. (2019) reported that nearly 50% of hypertensive individuals in India are unaware of their condition, and only one in ten has their blood pressure under control. This highlights the urgent need for effective interventions to improve hypertension management in the country.

Managing hypertension requires a combination of lifestyle modifications, regular blood pressure monitoring, and medication adherence. Research has demonstrated that self-monitoring blood pressure can reduce systolic BP by 2–8 mmHg (
Chobanian et al., 2003;
Tucker et al., 2017). However, traditional healthcare systems often fail to provide adequate support for self-management, particularly in resource-limited settings. In this context, mobile health (mHealth) applications have emerged as a promising tool to support patients in managing their conditions. mHealth refers to using mobile devices such as smartphones and tablets to provide healthcare services remotely (
Santo & Redfern, 2019). These applications can integrate self-monitoring tools (e.g., blood pressure tracking, step counting), alerts and reminders (e.g., medication adherence, follow-up visits), personalised health information (e.g., diet plans, educational materials), and feedback from healthcare providers to enhance self-care and disease management (
Alessa et al., 2018).

Despite the increasing adoption of mHealth applications, most existing solutions in India lack customisation to the local population’s needs. Many available apps are designed for Western healthcare settings, leading to usability and accessibility challenges for Indian users (

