Where n = number of subjects per arm, δ = effect size, σ = standard deviation, m = cluster size, ρ = intraclass correlation coefficient.

Based on systematic review evidence demonstrating that comprehensive mHealth interventions (combining self-monitoring, medication reminders, and lifestyle support) achieve systolic BP reductions of 4-6 mmHg compared to usual care (
Mekonnen et al., 2022;
Chandrasekhar et al., 2021), we anticipate a conservative effect size of 5 mmHg reduction in systolic BP. Assuming a baseline systolic BP of 145 ± 15 mmHg in our population (
Kumar et al., 2020), a five mmHg reduction represents a clinically meaningful 3.4% decrease. With 90% power, 5% significance level (two-sided), design effect of 1.45 (ICC = 0.05), and accounting for 15% attrition, the required sample size is 118 participants per arm distributed across 12 clusters of approximately 20 participants each (total n = 236). A sensitivity analysis confirms adequate power (>80%) to detect systolic BP reductions as small as 3.5 mmHg, ensuring the study can identify clinically meaningful effects consistent with published mHealth intervention studies.

Randomization will be carried out at the cluster level i.e. the villages would be the units of randomization. The entire process of randomization will be carried out by non-participating biostatistics faculty. Sequence generation will be done according to the block technique, with a block size of 4 for 2 allocation categories: ‘A’ for the new intervention and ‘B’ for the standard intervention, yielding 6 different combinations or sequences. Allocation concealment will be achieved through coded opaque sealed envelopes. Thereafter, the interventions will be allocated to the recruited clusters by the investigators strictly according to the sequence of the block. Each of the 3 steps of randomization, namely, sequence generation, allocation concealment, and implementation will be carried out by an independent faculty.

For the participants in the intervention group, the mHealth application will be installed on their smartphones, and the required data will be entered by the primary investigator. A demo of the application features will be provided. Participants from the intervention group will also be given automated BP apparatus. Under established clinical guidelines, participants will receive comprehensive blood pressure measurement training (
Williams et al., 2018;

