Whelton et al., 2018). The orientation protocol will include: (1) timing specifications requiring BP measurement twice daily (morning: 6-10 AM, evening: 6-10 PM) with at least 12 hours between readings; (2) standardised measurement technique involving three consecutive readings taken 1-2 minutes apart, with the first reading discarded and the mean of the second and third readings recorded; (3) pre-measurement requirements including 5 minutes of quiet rest, avoiding caffeine/exercise 30 minutes prior, proper cuff placement directly on skin (not over clothing), and maintaining feet flat on floor with back supported; (4) technical specifications ensuring appropriate cuff size selection and proper arm positioning at heart level; and (5) data entry protocols for recording measurements in the mHealth application immediately after each session. Participants will demonstrate competency in the BP measurement technique before the study commences, with refresher training provided at monthly follow-up contacts. The control group will receive standard care which includes advice to adhere to their prescribed medication and lead an active lifestyle. Baseline measurements like blood pressure, knowledge and practice of management of blood pressure, self-efficacy, and health status will be obtained from the recruited participants in both groups. Blood pressure will be measured with an electronic BP apparatus ([name] BP monitor-118), which will be calibrated periodically. Knowledge and practice will be assessed using a hypertension fact questionnaire. Self-efficacy using Medication Adherence Self-Efficacy Scale (MASES) and Self-Efficacy for Managing Chronic Disease 6-item Scale will be assessed and health status using SF-36 questionnaire will be assessed for pre and post-test (
Fernandez et al., 2008;
Lorig et al., 2001;
Ware & Gandek, 1998). For any reason, if the participant is unable to use the application, we will be discontinuing the intervention regimen for that participant. Regular phone calls will be made to remind them to use the application and to track their BP. The participants will be allowed to withdraw from the study at any given time as per their decision. The consort flowchart of the phase 3 is shown in
Figure 4.

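### The blood pressure monitor is both an unconditional part of the intervention and a compliance reward with no stated arm or timing; the two statements must be reconciled

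*Protocol article*

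**What the plan says.** In the Protocol article, Methods, Phase 3, the device is part of the intervention package: "Participants from the intervention group will also be given automated BP apparatus". No compliance condition is attached. The same section builds home measurement on the device, with "timing specifications requiring BP measurement twice daily" and a competency check before the study starts. For the comparator it says: "The control group will receive standard care which includes advice to adhere to their prescribed medication and lead an active lifestyle". No monitor is mentioned for controls.

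Under Potential strengths and limitations, the article says that loss to follow-up will be kept low by "strategic incentives, such as providing blood pressure monitors to participants who demonstrate compliance with the study protocol". It does not say which arm this covers, when the monitor is handed over, or how it relates to the device already issued to the intervention group.

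The article treats self-monitoring as active in three places. The abstract states: "Evidence supports that self-monitoring and blood pressure self-management can lower systolic BP by an average of 3.2 mmHg". The Introduction says that "self-monitoring blood pressure can reduce systolic BP by 2–8 mmHg". The Phase 3 eligibility text calls for stratifying people who already measure regularly, because that habit may affect how well the intervention works.

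**The concern.** The same kind of device is given to the intervention arm at the outset in one section and is a reward to be earned in another. Staff following the article could act on the second statement in ways that affect the primary comparison of systolic pressure.

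- **Controls earn a monitor during follow-up.** They would then hold an active component of the intervention, and the difference between arms could shrink.
- **Intervention participants must earn their monitor.** This contradicts the unconditional provision in Phase 3 and the twice-daily measurement that depends on it.
- **Retention differs by arm.** In the intervention arm, compliance plausibly means using the app and measuring twice daily. In the control arm it can mean little more than attending assessments. A reward tied to it may hold the arms differently. The article plans for 15% attrition and relies on intention-to-treat analysis with multiple imputation, and arm-dependent dropout could bias that analysis.

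**Working it through.** **Step 1: the statements side by side**

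| | Methods, Phase 3 | Potential strengths and limitations |
|---|---|---|
| Who receives a monitor | Intervention group | Participants, arm not named |
| Condition | None | Compliance with the protocol |
| When | At set-up, since training and twice-daily measurement depend on it | Not stated |
| Purpose | Part of the intervention | Reducing loss to follow-up |

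**Step 2: which readings fit the incentive sentence**

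1. Controls receive a monitor during follow-up: fits the sentence and alters the control condition.
2. Intervention participants receive one only once compliant: fits the sentence and contradicts Phase 3.
3. A monitor is handed over after the last measurement: fits the sentence and adds no device to control care during follow-up.
4. Compliant intervention participants keep their device at the end: fits the sentence without contamination, but turns a device described as given into a conditional loan.

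Nothing in the article selects among these.

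**Step 3: how large dilution could be under reading 1**

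Inputs from the article:
- Planned difference: 5 mmHg (Phase 3, sample size: "we anticipate a conservative effect size of 5 mmHg reduction in systolic BP").
- Effect of self-monitoring: 2–8 mmHg (Introduction).
- Effect of self-monitoring plus self-management: 3.2 mmHg (Abstract).

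Assumptions, because the article gives neither:
- f, the share of controls who receive a monitor during follow-up.
- e, the effect of the monitor alone, taken from the figures above and assumed to be reached in full.

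Formula: remaining difference = 5 − f × e.

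| f | e = 2 | e = 3.2 | e = 8 |
|---|---|---|---|
| 25% | 5 − 0.5 = 4.5 | 5 − 0.8 = 4.2 | 5 − 2.0 = 3.0 |
| 50% | 5 − 1.0 = 4.0 | 5 − 1.6 = 3.4 | 5 − 4.0 = 1.0 |
| 100% | 5 − 2.0 = 3.0 | 5 − 3.2 = 1.8 | 5 − 8.0 = −3.0 |

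At f = 50% the loss is therefore 1 to 4 mmHg, and 1.6 mmHg with the abstract's figure. The upper end is a bound, not an expectation. A monitor effect above 5 mmHg would exceed what the whole package is planned to achieve, which is why the last cell is negative. With e capped at 5, the loss at f = 50% is 0.5 × 5 = 2.5 mmHg.

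**Step 4: why the result is left in mmHg**

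The stated 118 per arm does not follow from the stated inputs. For 5 mmHg, SD 15, 90% power and 5% two-sided, n = 2 × 15² × (1.960 + 1.282)² / 5² ≈ 189.1, so 190 per arm before design effect and attrition. Then 189.1 × 1.45 ≈ 274.2, and 274.2 / 0.85 ≈ 323. That is a separate matter, and power figures here would mix the two.

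**The case against.** A reader might infer that the dual role must either contaminate the controls or withhold the intervention. The documents do not support that. The incentive sentence sets no time, so a monitor given after the final assessment, or kept by intervention participants at the end, fits it too. It also offers monitors only as an example, in a discussion of limitations and not in the description of the intervention. The sentence just before it concerns adherence supported by calls and push notifications, which points towards the app arm. Nowhere does the article say that controls receive a monitor during follow-up. All of this stands.

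A reader might also infer that attrition will differ by arm. That is possible but not shown: the list of incentives is open, and others for controls are not excluded.

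The 3.2 mmHg figure should not be read as the effect of a monitor. The article attributes it to self-monitoring and self-management together. A control given a device would not thereby receive the app, its reminders and education, or the measurement training. A monitor earned part-way would also act for only part of follow-up. This too stands, and it makes the mmHg figures illustrative.

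Nor does the incentive necessarily destroy a comparison of the app with standard care. The planned contrast was always a package of app, device, training and calls, and a monitor handed over after the last measurement leaves it intact.

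The objection does not remove the conflict itself. A condensed article may leave incentive logistics to a full protocol, but here it makes a positive statement that does not fit its own description of the intervention. Loss to follow-up concerns both arms, and intervention participants already have a monitor, so the harmful reading is not far-fetched.

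**Conclusion.** The point holds as a conflict in the text that carries a risk to the primary contrast. The article issues the monitor unconditionally to one arm, and elsewhere makes the same kind of device a reward for compliance without naming arm or time. Dilution through controls, a conditional intervention and arm-dependent retention are each possible consequences; none is established.

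If half the controls were affected, the planned 5 mmHg difference would fall to between 4.0 and 1.0 mmHg across the article's 2–8 mmHg range, or to 3.4 mmHg with the abstract's figure. This rests on an assumed share of controls and an assumed device-only effect reached in full. If monitors are handed over only after the final measurement, dilution from this source is zero. The wording should be corrected, because the risk is real and removing it costs little.

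**What to change.** Revise the incentive sentence under Potential strengths and limitations, and align it with Methods, Phase 3, so that the article states:

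- Intervention participants receive the monitor at the start regardless of compliance, as Phase 3 already says.
- Any monitor for control participants is given only after their final outcome assessment, for attending it and not for compliance.
- Any retention incentive during follow-up is the same in both arms and is not a blood pressure device.

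The cost is a change of wording plus a modest outlay for end-of-study monitors, or another token, for controls. Whether that outlay is already budgeted cannot be told, because the article does not say that the present incentive covers controls.

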## Conclusion

Using mHealth applications for remote monitoring and self-management helps reduce the burden on health-service system. In the proposed research, we will be developing an mHealth application for people with hypertension to meet the local health information needs, provide information in regional language and will be designed based on patient usability feedback. The application will monitor blood pressure, physical activities, medication, diet, and provide recent updates on hypertension management. This application, if found effective, can improve the health status, knowledge, and self-care approach among hypertensive patients by installing the mHealth application. Additionally, it may even minimize the problems caused for accessing healthcare due to the recent pandemic and can be the solution to evade in-person sessions.

Future research should validate this intervention across multiple Indian states, incorporating diverse languages, cultural practices, and healthcare infrastructure variations to establish broader generalizability across India’s heterogeneous population. A multi-state consortium approach could facilitate the development of a scalable mHealth platform with modular language and cultural components, ultimately contributing to nationwide hypertension management improvement. Economic evaluation studies across different socioeconomic contexts would also further inform policy decisions regarding mHealth implementation at scale.

## Data Availability

No underlying data are associated with this article. figshare: FGD guide.
https://doi.org/10.6084/m9.figshare.21463152.v1 (
[name], 2022a). figshare: Interview guide.docx.
https://doi.org/10.6084/m9.figshare.21485901.v1 (
[name], 2022b). Data are available under the terms of the
Creative Commons Attribution 4.0 International license (CC-BY 4.0). figshare: SPIRIT checklist for ‘Effectiveness of an mHealth application on remote monitoring and self-management of persons with hypertension in a coastal taluk of Udupi district: A study protocol’.
https://doi.org/10.6084/m9.figshare.21485946.v1 (
[name], 2022c).
